### Implementation strategies and components

#### Electronical tools

Based on a sounding board discussion, we designed and optimized the different electronical study tools in collaboration with the technical providers. In addition, we defined and implemented a structured data export, first, to guarantee user’s compliance measurement during study time, second, to enable adoption of tool items during the implementation period based on preliminary analyses, and, third, to establish a patient-oriented data “cockpit” for benchmarking.

#### User-oriented key data benchmarking

Based on the sounding board consensus, we designed a structured questionnaire (see Additional file 2) to perform phone interviews with all included patients 30 days after hospital admission to assess their outcome data and satisfaction. Each study site establishes a local interview team performing the 30-day structured follow-up interviews. Depending on the cumulative number of patients, between 3 and 7 part-time working persons were recruited by each study site, respectively, and were finally instructed by the core study nurse team.

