### Data collection process

The study period is divided into three 6-month phases, whereas the observation and the intervention phase until the end of January 2019 are season-matched, interrupted by a run-in non-season-matched implementation phase. The period of “In-HospiTOOL” implementation in the participating hospitals will be devoted to technical implementation, training of involved study personnel, nurses, social workers, physicians, and pilot testing. We will collect data throughout all three study periods by using electronic medical records and will contact all patients 30 days after hospital admission by phone interview. Data from the structured phone interviews will be stored on a data base using the secuTrial© software (secuTrial®; interActive Systems GmbH, Berlin, Germany).

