### Endpoints

All patients will be daily assessed during hospitalization and contacted 30 days after admission by phone for a structured and blinded interview to assess primary and secondary endpoints.

The primary endpoint of this study is length of hospital stay within 30 days after admission including readmissions during this period (corresponding to Module 1). Length of hospital stay will be verified based on hospital data for the index hospital stay and complemented by 30-day interviews regarding possible secondary hospitalizations.

Secondary endpoints (corresponding to Module 1–3) include measures of patient-oriented outcomes:in-hospital and all-cause 30-day mortalityunplanned readmissions or unplanned general practitioner / ED visitsdelaying factors of ED- and medical ward’s floweffective time to hospital discharge after involving external institutions (time from transfer application to transfer)institutionalizationsatisfaction with ED-, ward-, and discharge processfunctional status (incl. Quality of life) using the EuroQol Group 5-Dimension Self-Report Questionnaire (see Additional file 1) [23].

To study hospital internal processes and effects of interprofessionality, we will look at compliance and agreement of the three health professions (physicians, nursing, and social workers) in the use of “In-HospiTOOL”, and delays from the anticipated to the effective discharge date as compared to discharge date anticipated by the different health care professionals on admission and during the course of the hospital stay. We will use the above-mentioned outcome data set as benchmark to establish a risk-adjusted resource and quality cockpit to compare different hospitals and demographics (corresponding to Module 3).

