### Statistical analysis plan and sample size

The primary analysis population includes all consecutively recruited patients following an intention-to treat (ITT) principle. The number of patients lost to follow-up will be minimized by every effort. The per-protocol (PP) population analysis will be prospectively defined to exclude patients in whom major protocol violations have occurred. Specifically, the following criteria will lead to exclusion from the PP population: major violation of study inclusion or study exclusion criteria, patients with missing information from the In-HospiTOOL forms, or missing follow-up interviews.

We will compare all endpoints between all three study phases in the overall ITT population, the PP population and within predefined subgroups as discussed below. We will analyze all endpoints in an adjusted manner for the main covariates such as age, gender, health care insurance, home of residence, main diagnosis, comorbidities, and study center. Regarding sample size considerations, we include consecutive patients in each hospital over a 6-month period for the observation, implementation, and the intervention period, respectively. Given the large number of patients per study site seen in routine (i.e. between 2`500 and 8`000 polymorbid medical inpatients) per year, we estimate to enroll approximately ~ 35′000 patients over 18 months of recruitment. This large amount of patient data will provide adequate power to investigate the effect of introducing a patient care tool in the overall medical hospitalized patient population and allow for subgroup analyses, as well as important post-hoc analyses.

We will perform two complementary, quasi-experimental analyses to estimate the effect of the intervention: difference in differences and ITS.

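### Readmission days in the primary endpoint, and apparently deaths after discharge, depend on a day-30 phone call that affected patients are plausibly less likely to answer, so these harms are liable to be under-counted

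*Protocol article*

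**What the plan says.** The primary endpoint (Endpoints) is "length of hospital stay within 30 days after admission including readmissions during this period". The same section states the source of each part: length of stay is to be "verified based on hospital data for the index hospital stay and complemented by 30-day interviews regarding possible secondary hospitalizations". More generally, patients are assessed daily in hospital and then "contacted 30 days after admission by phone for a structured and blinded interview to assess primary and secondary endpoints". The secondary endpoints include all-cause 30-day mortality, unplanned readmissions, and unplanned visits to an emergency department (ED) or general practitioner.

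The section User-oriented key data benchmarking repeats the role of the call: staff are to "perform phone interviews with all included patients 30 days after hospital admission to assess their outcome data and satisfaction".

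Electronic records are also available. Data collection process says: "We will collect data throughout all three study periods by using electronic medical records". The article does not say that these records are used for events after the index stay.

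On missing interviews, Statistical analysis plan and sample size excludes from the per-protocol population "patients with missing information from the In-HospiTOOL forms, or missing follow-up interviews". It also says: "The number of patients lost to follow-up will be minimized by every effort". It gives no expected contact rate.

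**The concern.** The hypothesis under Module 1 is a shorter stay without worse patient outcomes. The natural risk of discharging earlier is harm after discharge, and that is the part of follow-up assigned to the phone call. A patient who has died, is back in hospital or has moved to a facility is plausibly less likely to complete an interview on day 30. So is a patient with cognitive impairment, which the Background names as a risk factor. Missing data would then depend on the outcome itself.

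Three consequences follow.

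- Index days and in-hospital deaths are observed directly, while later days and deaths may be observed only in part. If the tool moves events from before to after discharge, the observed totals can fall without any true fall.
- A change in contact rate between phases can look like a change in hospital days. The external controls would not cancel it, because they come from Federal Statistical Office data (Control population) and no interview is described for them.
- The per-protocol exclusion of missing interviews selects on the same events.

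**Working it through.** **Plan's own figure.** There is none to reproduce. The article states no contact, readmission or mortality rate. All rates below are assumptions that show mechanism and scale.

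**Step 1: shortfall in readmission days.** Assume 80% of patients are reached, 8% of the reached and 16% of the unreached are readmitted, and each readmission lasts 7 days.

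- True days per patient: 0.80 × 0.08 × 7 + 0.20 × 0.16 × 7 = 0.448 + 0.224 = 0.672. The overall readmission rate is 0.064 + 0.032 = 9.6%.
- Unreached patients scored as zero: 0.448. Shortfall 0.224 / 0.672 = 33%.
- Reached patients only: 0.08 × 7 = 0.56. Shortfall 0.112 / 0.672 = 17%.

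**Step 2: spurious difference between phases.** Hold the true rate at 9.6% (0.672 days) in both phases and the rate among the unreached at 16%. Let contact be 85% in one phase and 75% in the other.

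| | 85% reached | 75% reached | Difference |
|---|---|---|---|
| Missed days (share unreached × 0.16 × 7) | 0.168 | 0.280 | 0.112 |
| Observed, unreached scored as zero | 0.504 | 0.392 | 0.112 |
| Observed, reached only | 0.504 / 0.85 = 0.593 | 0.392 / 0.75 = 0.523 | 0.070 |

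The phase with lower contact appears to have fewer hospital days although nothing has changed.

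The result depends on what is held fixed. If 8% and 16% are kept in both phases instead, zero scoring gives 0.85 × 0.08 × 7 = 0.476 against 0.75 × 0.08 × 7 = 0.420, a difference of 0.056. Reached patients show 0.56 in both phases, so no difference. But the true values are then 0.644 and 0.700, so that setting is not one of no true change.

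**Step 3: dilution of a harm in deaths after discharge.** Let p be the true rate, r_e the response rate with an event and r_n the response rate without. Among responders the observed rate is p·r_e / (p·r_e + (1 − p)·r_n). Take r_n = 80% and true rates of 3% and 4%, a difference of 1.0 point.

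| r_e | Observed rates | Observed difference (points) |
|---|---|---|
| 80% | 3.00% and 4.00% | 1.00 |
| 60% | 2.27% and 3.03% | 0.76 |
| 40% | 1.52% and 2.04% | 0.52 |
| 20% | 0.77% and 1.03% | 0.26 |

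With equal capture in both phases the ratio stays close to 4/3, but the absolute difference shrinks. If response does not depend on the event, there is no bias among responders.

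**Step 4: what records could recover.** If records capture a share s of events and the call captures 40% to 60% of the rest, total capture is s + (1 − s) × 0.4 to s + (1 − s) × 0.6. That is 40% to 60% at s = 0, 70% to 80% at s = 0.5, and 88% to 92% at s = 0.8. The article does not give s.

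**The case against.** The strongest reply is that the article does not limit itself to the call. The wording on length of stay adds the interview to hospital data without excluding records, and electronic records are collected in all three phases. Enrolment is consecutive, so a medical readmission to the same hospital, and a death during it, should ordinarily appear in that hospital's data. A call to a household can reveal that a patient has died or is in hospital. Rules on proxies, repeat calls and missing interviews may sit in the full protocol, the analysis plan or the questionnaire, none of which is shown.

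Much of this stands as a limit on what can be claimed. A reader might infer that harms are certain to be under-counted; without a contact rate the documents support only a liability. A reader might infer that deaths after discharge come from the interview alone; only later hospitalizations have an explicit source rule, and the source for deaths follows from a general sentence. A reader might also infer that a missing interview counts as no event; the article states only the per-protocol exclusion, so the 33% shortfall is conditional on zero scoring.

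The reply does not remove the point. The article does state a source rule: hospital data for the index stay, interview for what follows. Nowhere does it assign the records to events after the index stay, and the absence of proxy or tracing rules is not part of this point.

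**Conclusion.** The point holds as a weakness in a stated choice of data source. Readmission days in the primary endpoint rest on the day-30 call, and 30-day deaths appear to. If patients with events are harder to reach, both are under-counted in a direction that favours a conclusion of no harm. Under the assumed rates, readmission days are short by 17% (reached patients only) to 33% (unreached scored as zero). A 10-point difference in contact between phases, with no true change, produces a spurious difference of about 0.07 to 0.11 days.

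These sizes rest on three assumptions: the readmission rate among the unreached is twice that among the reached, readmissions last 7 days, and neither records nor proxies recover the missed events. Any recovery reduces them. Relative comparisons are roughly preserved if capture is equal in every phase; absolute differences are not.

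**What to change.** Change the source order in the Endpoints section:

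- Take readmissions, readmission days, ED visits and deaths up to day 30 first from the electronic records of the seven study hospitals, for every included patient, whether or not the interview succeeds.
- Use the interview for events elsewhere.
- Do not count a missing interview as no event.
- Report contact rates by phase.

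The cost is an additional record query and patient-level linkage of later episodes to the index stay. The structured export described under Electronical tools serves compliance measurement, tool adaptation and benchmarking, so this linkage is real extra work. Events at institutions outside the study will remain incomplete for patients who are not reached.

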#### Coaching

Before starting the implementation phase, a minimum of two interprofessional onsite visits at each study site ensures full information and compliance of the local staff (physicians, nurses, social workers, therapeutic disciplines) about participating in the In-HospiTOOL study and preparing them how to use the newly designed electronical study tools in the later implementation phase. Before and during the intervention phase, a minimum of two interprofessional onsite visits at each study site will be repeated to guarantee an optimal monitoring quality and a high usability. To guarantee a standardized staff education, we designed (in cooperation with the “Berner Bildungszentrum Pflege”) and provide a teaching video to all study sites, where the appropriate usage of the electronical study tools has been described comprehensively (https://youtu.be/bNyRPucs-FQ). To finally guarantee a maximal utilization and a correct application in daily clinical routine, we encourage all the study sites to introduce a local supervisor. The local supervisor will monitor compliance of the In-HospiTOOL usage, such as the physician’s initial assessment, PACD score, Visitentool (on weekdays), reengineered discharge form, and intervenes if appropriate. The required profiles of personnel qualification are assertiveness and well-experienced clinical nurses, nursing experts with clinical background, or case managers.

### Statistical analysis plan and sample size

The primary analysis population includes all consecutively recruited patients following an intention-to treat (ITT) principle. The number of patients lost to follow-up will be minimized by every effort. The per-protocol (PP) population analysis will be prospectively defined to exclude patients in whom major protocol violations have occurred. Specifically, the following criteria will lead to exclusion from the PP population: major violation of study inclusion or study exclusion criteria, patients with missing information from the In-HospiTOOL forms, or missing follow-up interviews.

We will compare all endpoints between all three study phases in the overall ITT population, the PP population and within predefined subgroups as discussed below. We will analyze all endpoints in an adjusted manner for the main covariates such as age, gender, health care insurance, home of residence, main diagnosis, comorbidities, and study center. Regarding sample size considerations, we include consecutive patients in each hospital over a 6-month period for the observation, implementation, and the intervention period, respectively. Given the large number of patients per study site seen in routine (i.e. between 2`500 and 8`000 polymorbid medical inpatients) per year, we estimate to enroll approximately ~ 35′000 patients over 18 months of recruitment. This large amount of patient data will provide adequate power to investigate the effect of introducing a patient care tool in the overall medical hospitalized patient population and allow for subgroup analyses, as well as important post-hoc analyses.

We will perform two complementary, quasi-experimental analyses to estimate the effect of the intervention: difference in differences and ITS.

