## Methods/design

### Aim and study design

The “In-HospiTOOL” study is a quasi-experimental investigator-initiated, multicenter effectiveness trial investigating the effects of a new patient in-hospital management tool to improve length of hospital stay and other outcomes using an ITS model. The overall 18-month study time is divided in a 6-month observational phase, a 6-month implementation phase, and a 6-month intervention phase.

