### Independent variables

The primary exposure variable of interest is the intervention, i.e. the implementation of the “In-HospiTOOL”. As outlined in the statistical plan, we will adjust our model to the following covariates: demographics (age, gender, health care insurance, home of residence [home versus facility]), main diagnosis (grouped using the “International Classification of Diseases (ICD-10)” [24]), comorbidities (using the Elixhauser comorbidity index [19]), and study center.

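### The per-protocol rule requires completed tool forms, which observation-phase patients cannot have, so the planned per-protocol comparison between phases has no usable baseline as written

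*Protocol article*

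**What the plan says.** All references are to the protocol article.

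- **PP rule** (Statistical analysis plan and sample size). Besides major eligibility violations, the grounds for exclusion are "patients with missing information from the In-HospiTOOL forms, or missing follow-up interviews". No phase is named.
- **Use of PP** (same section, next paragraph). "We will compare all endpoints between all three study phases in the overall ITT population, the PP population", and within subgroups. ITT is named as the primary population.
- **Phases** (Aim and study design). The study is "divided in a 6-month observational phase, a 6-month implementation phase, and a 6-month intervention phase".
- **When the tool arrives** (Data collection process). The implementation period "will be devoted to technical implementation, training of involved study personnel, nurses, social workers, physicians, and pilot testing".
- **When staff start using it** (Coaching). Site visits before implementation serve to inform staff, "preparing them how to use the newly designed electronical study tools in the later implementation phase".
- **What the exposure is** (Independent variables). "The primary exposure variable of interest is the intervention, i.e. the implementation of the" tool.
- **Interviews** (Data collection process; User-oriented key data benchmarking). A telephone interview 30 days after admission is planned for all patients in all three phases.
- **Endpoints** (Endpoints). The primary endpoint is days in hospital within 30 days, including readmissions. The index stay is verified from hospital data, and the interview adds later admissions. All-cause 30-day mortality is a secondary endpoint.

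**The concern.** A population used to compare periods before and after an exposure has to be defined by something that can be observed in both periods. Form completion is part of the exposure. Used as a membership rule, it either removes the baseline or, if waived there, filters the later patients on a post-exposure process that the baseline was not filtered on. The primary endpoint is length of stay, and whether a full set of forms gets completed may well depend on how long the patient stays. The planned adjustment covers baseline characteristics and study center, so it would not remove selection of that kind.

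The interview criterion is a separate matter. It applies in all phases and so does not empty the baseline. But it decides who enters a mortality comparison by an event at day 30, which patients who have died cannot attend.

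At stake is a planned secondary analysis of every endpoint. It either cannot be run as written, or could agree or disagree with ITT for reasons unrelated to the tool.

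**Working it through.** **1. Enrolment, used only for scale.** Seven hospitals with 2,500 to 8,000 patients a year over 1.5 years give 7 × 2,500 × 1.5 = 26,250 to 7 × 8,000 × 1.5 = 84,000. The stated figure of about 35,000 lies inside this range. Spread evenly, it is 35,000 / 3 ≈ 11,667 per phase. The article gives no form-completion rate, interview-response rate, or mean or SD of stay. Every such value below is an assumption.

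**2. The rule read literally.** PP count in a phase = N × P(forms complete) × P(interview complete).

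- Observation: P(forms complete) = 0, so 11,667 × 0 = 0.
- Intervention, both rates assumed between 60% and 90%: 11,667 × 0.60 × 0.60 ≈ 4,200 to 11,667 × 0.90 × 0.90 ≈ 9,450.

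That forms are absent in the observation phase is inferred from the timing of implementation and training and from the tool being the exposure. It is not stated outright, but nothing in the article contradicts it for the forms.

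**3. The form criterion waived in the observation phase.** The baseline becomes 11,667 × 0.60 to 0.90 ≈ 7,000 to 10,500 patients, filtered on interviews only. Later patients are filtered on interviews and forms. With no true effect, the PP difference equals the mean stay of form-complete patients minus the mean stay of all patients. Interview completion is taken as unrelated to stay.

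*Assumption set A:* gamma-distributed stay, mean 7.0 days, SD 5.7. Mean below the median is 2.85 days, above it 11.15. Form completion is p_S below the median and p_L above it, averaging 75%; interview completion is 75%.

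Bias = (p_S × 2.85 + p_L × 11.15) / (p_S + p_L) − 7.00

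- 75% / 75%: 0
- 80% / 70%: (2.28 + 7.81) / 1.50 − 7.00 = −0.28 days
- 85% / 65%: −0.55 days
- 90% / 60%: −0.83 days
- With the pattern reversed, the same sizes to within rounding, with a positive sign

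Patient-level SE = 5.7 × √(1/8,750 + 1/6,563) ≈ 0.09 days. A bias of 0.28 days is about three of these. The SE ignores clustering within seven hospitals, which would enlarge it.

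*Assumption set B:* lognormal stay (median parameter 6, sigma 0.8, rounded up to whole days), mean 8.77, SD 7.8. 19% stay 3 days or fewer (mean 2.50 days); the rest average 10.26.

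- Forms missing in 15% of short stays and 10% of others: +0.07 days
- 30% and 10%: (0.1925 × 0.70 × 2.50 + 0.8075 × 0.90 × 10.26) / (0.1925 × 0.70 + 0.8075 × 0.90) − 8.77 = +0.28 days
- 50% and 10%: +0.59 days
- Forms missing instead in 20% of stays of 10 days or more and 10% of others: −0.29 days
- 30% and 10% on that same split: −0.61 days

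Patient-level SE of a difference between two full phases: 7.8 × √(2/11,667) ≈ 0.10 days.

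The sign depends on whether short or long stays lack forms, and the size on how unequal completion is.

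**4. Interviews and mortality.** PP membership needs an interview, the interview takes place 30 days after admission, and PP is to be used for all endpoints, including 30-day mortality. If death before day 30 makes the interview missing, those deaths leave the PP population. If a contact that establishes death counts as completed, they stay. The article does not say which applies.

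**The case against.** The strongest reply is that ITT is primary and untouched, the article gives PP no confirmatory role, and the authors evidently meant forms to be required only where forms exist. One clarifying clause might suffice, and some selection is a known limit of any PP analysis. The point about the primary result stands and limits how serious this is. The clarifying clause does not settle the matter: step 3 of the check is exactly that reading, and it leaves the two sides of the comparison filtered differently. Nor is this detail left to a separate analysis plan. The article lists the criteria and states the comparison.

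A reader might also infer several stronger things that the article does not support:

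- *That PP is empty until the intervention phase.* Only the observation phase follows from the text. Implementation includes pilot testing, so some forms may exist then.
- *That the baseline would be wholly unselected.* It would still be filtered on interviews.
- *That the external controls drop out too.* The PP comparison is described between study phases, and nothing applies the PP rule to the Federal Statistical Office data.
- *That short weekend stays fail by design, because the ward-round tool is listed as "Visitentool (on weekdays").* That phrase describes the usage a local supervisor monitors. If entries are expected only on weekdays, a weekend without one is not missing information.
- *That the bias has a known direction.* Short stays leave less time for forms, while long stays with daily reassessment give more chances to miss one.
- *That PP mortality must fall towards zero.* This depends on how a contact establishing death is classified.

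**Conclusion.** The point holds in limited form. As written, the form criterion and the planned three-phase PP comparison cannot both be carried out, because the observation phase contributes no patients. This rests on the inference that forms did not exist before implementation. Waiving the criterion there makes the comparison possible but open to bias of unknown sign. The bias is zero if completion is unrelated to stay, and roughly 0.3-0.8 days under the more unequal completion rates assumed above, against a patient-level SE of about 0.1. Those rates and the stay distributions are illustrations, not figures from the article. The effect of the interview criterion on PP mortality is conditional on a definition that the article does not give. The primary ITT analysis is unaffected, so this should be fixed but is not a threat to the main conclusion.

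**What to change.** 1. Drop form completion as a condition of PP membership for the comparison between phases. Keep only criteria that can be judged the same way in every phase, such as eligibility violations.
2. Report adherence to the tool separately, for example as form-completion rates by hospital and week, with all patients kept. The structured data export described under Electronical tools is already meant to measure user compliance.
3. Do not let a missing interview exclude a patient from PP analyses of mortality or of length of stay known from hospital data. State how a contact that establishes death is classified. Where the interview is the only source, as for later admissions, treat its absence as missing data for that component.

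Cost: a change of wording and a little more analysis for the adherence report, with no new data collection. The price is that PP then reflects adherence less directly.
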